## Abstract

**Background:**

Discussing deceased organ donation can be difficult not only for families but for health professionals who initiate and manage the conversations. It is well recognised that the methods of communication and communication skills of health professionals are key influences on decisions made by families regarding organ donation.

**Methods:**

This multicentre study is being performed in nine intensive care units with follow-up conducted by the Organ and Tissue Donation Service in New South Wales (NSW) Australia. The control condition is pre-intervention usual practice for at least six months before each site implements the intervention. The COMFORT intervention consists of six elements: family conversations regarding offers for organ donation to be led by a “designated requester”; family offers for donation are deferred to the designated requester; the offer of donation is separated from the end-of-life discussion that death is inevitable; it takes place within a structured family donation conversation using a “balanced” approach. Designated requesters may be intensivists, critical care nurses or social workers prepared by attending the three-day national “Family Donation Conversation” workshops, and the half-day NSW Simulation Program. The design is pre-post intervention to compare rates of family consent for organ donation six months before and under the intervention. Each ICU crosses from using the control to intervention condition after the site initiation visit. The primary endpoint is the consent rate for deceased organ donation calculated from 140 eligible next of kin families. Secondary endpoints are health professionals’ adherence rates to core elements of the intervention; identification of predictors of family donation decision; and the proportion of families who regret their final donation decision at 90 days.

**Discussion:**

The pragmatic design of this study may identify ‘what works’ in usual clinical settings when requesting organ donation in critical care areas, both in terms of changes in practice healthcare professionals are willing and able to adopt, and the effect this may have on desired outcomes. The findings of this study will be indicative of the potential benefits of the intervention and be relevant and transferrable to clinical settings in other states and countries.

**Trial registration:**

Australian New Zealand Clinical Trials Registry (ANZCTR): ACTRN12613000815763 (24 July 2013). ClinicalTrials.gov: NCT01922310 (14 August 2013) (retrospectively registered).

**Electronic supplementary material:**

The online version of this article (doi:10.1186/s12913-016-1964-7) contains supplementary material, which is available to authorized users.

## Background

Organ and tissue transplantation is the definitive treatment for people with a wide range of end-stage organ failures. Escalating worldwide demand continues to drive efforts in many countries to increase the rate of deceased organ donation [1]. In Australia in 2011 the annual rate of deceased organ donation (15.1 donors per million population, dpmp) was below similar countries in the developed world such as the United Kingdom (UK) (17 dpmp), and international leaders such as the United States of America (USA, 25.9 dpmp), and Spain (35.9 dpmp) [2].

In New South Wales (NSW), Australia, consent for organ donation must be provided either from the patient while living or, when incapacitated, from the senior available next-of-kin (SaNOK): that is, a relative identified in line with an agreed family hierarchy [3]. In NSW the annual consent rate increased from 51% in 2011 [4] to 62% in 2013 [*unpublished 2014 NSW Organ and Tissue Donation Service (OTDS) data*], contributing to an annual national increase from 57% [5] to 61% [6] respectively. Other countries with similar health systems such as the UK, also reported a national consent rate of around 60% for 2013/14 [7]. Yet this consent rate is comparatively low in contrast to overwhelming positive public opinion in surveys of the UK and Australian populations with 90% and 69% respectively supporting donation and willing to become organ donors, describing predominantly altruistic beliefs on the topic [7–9]. Furthermore the consent rate decreased to 29% *[unpublished 2011 NSW OTDS data]* when families have been offered organ donation at the hospital and the patient had not previously registered their donation decision.

Physicians need effective communication skills when approaching families regarding end-of-life decisions, and skill enhancement has been advocated to maximise the consent rate for deceased donation [10, 11]. The difficulty of raising the subject of organ donation has long been recognised. North American research revealed Intensive Care Unit (ICU) physicians were poorly prepared to understand grief reactions, missed opportunities to provide emotional support, and failed to listen to families and support informed decision-making [12–14]. In Australia, a one-day donor awareness program designed to increase health professional’s understanding of organ donation and to provide skills to sensitively conduct family donation conversations has been available since 1994 [15], with intensivists reporting this training as adequate preparation [16]. Despite that training, ICU nurses, intensivists and specialist donation nurses may avoid raising the topic due to their own perceptions of a family’s grief, fear or guilt, or of adding to a family’s distress [17, 18]. However, a longitudinal study of 49 relatives in the UK reported that discussing organ donation did not increase families’ distress [19].

The approach and skill of the health professional making the donation request has been shown to be a key influence on families’ donation decisions [20]. In countries that lead in this field such as Spain and the USA, health professionals working as transplant coordinators or organ procurement coordinators receive specialised communication training and make the initial approach to families [10, 21, 22]. In Australia, the managing intensivist traditionally leads donation discussions with introduction to the donation specialist nurse (DSN) subsequent to verbal agreement to organ donation. DSNs are trained in organ donation activities, but not necessarily in leading the conversation [23]. Many intensivists only participate in organ donation discussions a few times per year, providing limited opportunities to practice the necessary specialised communication skills [16].

### ‘Best practice’ family approach

Intensive care medicine professional organisations and health authorities in Australia and the UK provide practice guidelines for communication between families and health professionals during end-of-life care, including organ donation decisions [23, 24]. In Spain and the UK a ‘family approach’ has been recommended with the requesting conversation planned between the managing team and a Specialist Nurse-Organ Donation [10, 25]. Ensuring families understand that the patient has died or that death is inevitable before donation is raised is a key feature. The initial approach to the topic of donation has been identified as a pivotal point in the process because families often make their donation decision at that time [26].

Effective communication within a structured multidisciplinary family meeting, also termed ‘family conference’, has been recommended for ICU physicians to facilitate informed decision making based on the anticipated wishes of the patient rather than those of the patient’s relatives [27–31]. Meetings ideally require multidisciplinary team planning, a private location and effective communication techniques such as the use of everyday language, listening and acknowledging relatives’ emotions or opinions and demonstrating compassion verbally and through non-verbal techniques [23, 32]. In the USA communication approaches have moved from a “neutral” position towards organ donation towards one of “dual advocacy”. This entails use of positive language, equally presenting the needs of the donor family and people on transplant waiting lists, assuming that most people would want to help others by donation [33, 34]. Training organ procurement coordinators (*n =* 22) in effective communication techniques for requesting organ donation increased the consent rate in participating hospitals by 9.2%, over 2 years [22, 35]. Families who were certain of their organ donation decision reported that health professionals providing them with clear information and emotional support were key factors in helping them make decisions with which they remained comfortable over time [36].

Studies conducted in North America have shown some donation decisions were later regretted, and that this occurred more frequently when the decision was to decline donation. For example, of 285 relatives interviewed an average of 13 ± 9 days after death, only 4% (6/147) who had agreed to donation would later have preferred they had declined. By contrast, of those who declined donation, 27% (37/138) later wished they had agreed [37]. Decisional regret, where relatives either regretted their decision or were unsure they would make the same decision again, persisted up to 10 months after bereavement. A study of 199 relatives interviewed eight to ten months after death revealed decisional regret was more evident in those who declined (42%; 19/45) than agreed to donation (9%; 15/154) [36]. Decisional regret was more likely when organ donation was raised before relatives were informed of the patient’s death, and when the first approach was by a health professional who managed the patient’s care, before a formal request from a separate organ procurement team [37].

### Specialised communication training

In Australia, training in specialised communication for health professionals who offer donation has been a key component of a national reform agenda [38]. A national program of specialised training in family-centred communication regarding organ donation, developed in collaboration with the Gift of Life Institute (Philadelphia, USA), was introduced in October 2011 [39]. The revised program delivered in two modules over three days, incorporated face-to-face presentations of theory followed by practical training with role-play exercises [40]. This approach — the Organ and Tissue Authority (OTA) Family Donation Conversation (FDC) core and practical modules – (see Additional file 1) has been adopted as ‘best practice’; intensive care specialists and organ donation health professionals elect to attend, and the College of Intensive Care Medicine made completion of the core module a mandatory training requirement for intensive care trainees from 2014 [41]. However, role-play alone may not adequately replicate the emotional nature of donation conversations.

In NSW, training for health professionals selected as “designated requesters” to lead donation conversations has been supplemented by a simulation program [4]. Piloted in 2012 the program uses real donation scenarios with standardised relatives played by professional actors [42]. Health professionals are able to rehearse, review and reflect on their developing effective communication skills when offering donation in a protected learning environment, and thereby become more comfortable discussing these topics. These ‘best practice’ methods involving use of specialised requesters to lead deceased organ donation discussions with families are based on work from other countries adapted to but not formally tested in Australian conditions. This study will examine implementation of a ‘best practice’ family approach intervention and identify its effectiveness in terms of family consent rates, and later decisional satisfaction or regret.

## Methods/Design

### Aims and hypothesis

The aim of this study is to examine the process of organ donation decision-making, and to test whether changes in requesting practices change rates of family consent for organ donation and other family-based outcomes. A secondary aim is to examine whether changes in requesting practices result in increased satisfaction by families with their donation decision. The hypothesis for the trial component is that, compared to current usual practice, a ‘best practice’ family approach intervention will increase the family consent rate for deceased organ donation.

### Design

This is a pre-post intervention design where rates of consent for organ donation for at least six months before implementation of the program in each ICU will be compared to the rates of consent for organ donation under the intervention.

### Settings

The study will be conducted in the ICUs or locations such as Emergency Departments when the patient is managed by ICU health professionals, of nine metropolitan and rural hospitals in NSW, with follow-up conducted by the NSW OTDS.

### The COMmunication with families regarding ORgan and tissue donation after death in intensive care (COMFORT) intervention

The intervention is a modification of current standard practice procedures for offering donation to families of potential organ donors. There are six essential ‘best practice’ elements of the intervention:A designated requester has primary responsibility for discussions regarding organ donation with the family of a potential donor. Primary communication with families regarding end of life management and death remains the responsibility of the managing team.Designated requesters are volunteer intensivists, experienced critical care nurses, or social workers who have been deemed appropriate by the site principal investigator/ICU department head to undertake the role, and complete mandatory training (see Additional file 1). Up to six designated requesters are estimated to be required at each study hospital.The offer of donation is separated from the conversation where families are informed of the patient’s death. It is important the family have accepted the inevitability of death before donation is raised [25].If families raise the topic of organ or tissue donation, the managing health professional sensitively defers the first donation conversation to the designated requester.Donation conversations are conducted within the structure of a family meeting, based on evidence-based guidelines for high quality communication regarding end-of-life care [23, 28–30].The requester uses a ‘balanced approach’: information is provided in a proactive manner, using open-ended questions to encourage active participation of family members in discussion. Information is provided about the benefits of organ and tissue donation for both families and recipients [39].

Key features to which the multidisciplinary team and designated requesters are expected to adhere are set out in Table 1.

**Table 1 Tab1:**
[figure not shown]
Key adherence criteria for delivery of the ‘COMFORT’ intervention

The training provides designated requesters preparation and opportunities to practice elements three to six of the COMFORT intervention. Designated requester training requirements are completed subsequent to attending the Organ and Tissue Authority FDC core and practical modules and the NSW simulation workshop (see Additional file 1) [40, 42]. Subsequent attendance at the simulation workshop is required for annual refresher training for DSNs and social workers, and 18 monthly for intensivists, for the duration of the COMFORT study.

As the study intervention is a modification to health service delivery, it is led in each hospital by local specialist donation nurses and doctors. Education sessions are delivered as required to colleagues in the departments of emergency medicine, intensive care, neurosurgery and social work to support and provide information and feedback on the implementation process of the new intervention. Information is collected from and on the health professionals involved in each organ donation event to track intervention fidelity.

### Participants

Participants in this study are the families of patients who are potential deceased organ and tissue donors and the health professionals involved in each organ donation event. Members of the managing team identify a possible deceased organ donor who is apparently medically suitable for organ donation, and notify the donation specialist at the hospital or the OTDS. To be eligible for the study a donation event must meet all inclusion and no exclusion criteria as detailed below:

#### Inclusion criteria

Donation events identified by patients of all ages managed in the ICU or under the care of ICU health professionals, who are potential deceased organ and tissue donors. For the primary endpoint only, patients must not have registered their donation wishes.

#### Exclusion criteria

Donation events or patients who fulfil one or more of the following criteria:A patient who is not medically suitable for deceased organ and tissue donation;A patient who does not have a SaNOK to participate in donation conversations;An adult patient in the ICU who is able to provide first person consent for deceased donation, for example a patient with cervical spine injury;A patient who is suitable to donate only tissue after death.

### Endpoints

The primary endpoint for the study is the family consent rate for deceased organ donation where the potential donor had not previously registered their donation wishes.

Secondary endpoints are: health professionals’ adherence rates to core elements of the COMFORT intervention; identification of predictors of family donation decision; and the proportion of SaNOK who report they regretted their final donation decision at around 90 days after enrolment.

### Study outline

In line with usual practice, potential donors are identified, a registry check is performed to find any recorded preference regarding organ donation by the patient, and the process of assessing medical suitability is commenced (not necessarily in that order). In the COMFORT intervention condition the managing team is responsible for delivering the news of death, and contacts the donation specialist/designated requester to plan the approach to the family and initiate the donation offer (as above and Table 1). In the pre-intervention control condition, the donation conversation is managed by the healthcare professional(s) and processes are the usual practice in that setting. A chart of the study design and data collection periods is shown in Fig. 1. The site initiation visit is the point where hospitals crossover from the control to the intervention condition. In both groups families may take up to 72 h for a final donation decision.

**Fig. 1 Fig1:**
[figure not shown]
Chart of the study design and data collection periods. Shaded cells represent intervention periods; Blank cells represent control periods. Each cell represents a data collection point, except those with ‘X’ *N =* NSW Organ and Tissue Donation Service, f = follow-up interviews

Bereavement support provided by the OTDS Family Support Coordinator is offered to families who participated in the donation requesting conversation regardless of their final organ donation decision. Senior next of kin, or the delegated decision maker, who agrees to bereavement aftercare is invited to participate in the subsequent follow-up interview at day 90 after enrolment.

### Evaluation: data collection and management

#### Setting

To characterise and describe the setting, data recorded at the beginning and at completion of the study at each site include: number of hospital and ICU beds; categories (medical/surgical/paediatric) of patients admitted to the ICU; areas of specialty; medical, nursing and allied health staffing establishments and ratios; availability of private meeting rooms; frequency of multidisciplinary communication (ward rounds; and family meetings).

#### Current control

To describe practice for the ‘control condition’ i.e. pre-intervention details of donation events for the period of six months before each site implements the intervention and joins the program will be extracted retrospectively. Data will include: eligibility for deceased organ donation; patients’ date of birth, donation intent registered on their motor vehicle licence and the Australian Organ Donor Register; initiator of the donation conversation; family final donation decision, and outcome of the donation event.

#### Intervention period screening

A screening log is maintained at the OTDS of notification of patients who are apparently medically suitable for deceased organ donation during the study intervention period. DSNs routinely coordinate data collection at each hospital and forward completed forms to the OTDS for validation and consistency checks.

#### Donation events

A unique number is allocated to each potential organ donor at enrolment. Data from eligible potential donation events include donation pathway (i.e. brain or circulatory death), designation of initiator of the family donation conversation, donation intent on a register, and family donation decision. Also characteristics of potential donors such as: date of birth, gender, ethnicity, religion, primary event/cause of death, dates and times of ICU admission and death, commencement of retrieval surgery, and family contact details.

#### Family donation conversation

Adherence to elements of the family donation conversation is consecutively recorded on a case report form for each donation event by self-report from the observations of health professionals who participated in the meeting. Details include general features of a structured family meeting and specific topics discussed in the first meeting. The role of the ICU health professional who led the initial family donation conversation (termed the ‘requester’) is central to this process; their demographic, training and number of donation requesting conversations experiences in the preceding calendar year are collected by self report. Reporting is undertaken at the closure of the conversation to minimise potential recall bias. A consensus approach is used with equal weight given to each health professional’s observations. Completion of the case report form may extend to one week. The final donation decision by the family is recorded at conclusion of the process. Reasons stated by the family and/or perceived by the health professional for that decision at that time point will be noted. See Additional file 2 for the case report form.

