#### To address the secondary endpoints

Adherence to core elements of the intervention will be obtained via the case report form and rates calculated.The proportion of all next of kin who report they regretted their final decision either to consent or to decline donation at 90 days will be calculated with 95% Confidence Interval.Characteristics of the donation process including staff adherence to core elements of the intervention and demographic characteristics of the potential donor, senior next of kin and of the requester will be explored. Exploratory analysis using both univariate and multivariate regression methods will be used as needed. A *p-*value of < 0.05 will be considered statistically significant for retention in the multivariate model and only univariate variables with a *p-*value <0.20 will be considered for inclusion to the multivariate model.

Categorical data (e.g. details of gender, religion, ethnicity of patient and health care professional and reasons to consent or decline donation) will be summarised by frequencies and percentages. Continuous data (e.g. age, time in family meetings) will be summarised using the mean and standard deviation.

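### Topic-coverage items are recorded while the family may already be deciding, then used to predict that decision, so the exploratory model could report reverse causation as a predictor of consent

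*Protocol article*

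**What the plan says.** Under Family donation conversation, adherence is recorded for each donation event "by self-report from the observations of health professionals who participated in the meeting". Two kinds of item are named: "Details include general features of a structured family meeting and specific topics discussed in the first meeting". Reporting takes place when the conversation closes, to limit recall bias, although "Completion of the case report form may extend to one week". The outcome has its own time point: "The final donation decision by the family is recorded at conclusion of the process".

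The Background, under ‘Best practice’ family approach, calls the initial approach pivotal because "families often make their donation decision at that time". The Study outline allows longer: "In both groups families may take up to 72 h for a final donation decision".

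The Endpoints section makes identifying predictors of the family's decision a secondary endpoint. Under To address the secondary endpoints, the candidates are "Characteristics of the donation process including staff adherence to core elements of the intervention", together with demographic characteristics of the donor, next of kin and requester. Univariate p < 0.20 is needed for a variable to be considered for the multivariate model, and p < 0.05 for it to be retained. The analysis is called exploratory. Adherence enters as one class of variable: elements settled before the family answers are not separated from those that depend on how far the conversation went.

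**The concern.** A topic can be covered only while the conversation continues. If a family refuses at the start and the requester stops there, the remaining topics go undiscussed because of the refusal. Regressing the decision on topic coverage then finds an association even when no topic has any influence, and the model cannot tell whether coverage led to consent or refusal stopped coverage.

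Reporting at the close of the conversation does not help, because the association would arise with perfectly accurate, immediate reporting. The limitations in the Discussion do not mention it.

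What is at stake is interpretation. The Discussion presents the study as a way to learn what works in requesting donation and which features of best practice matter. A spurious coverage effect would point in the direction that the study hopes to find.

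**Working it through.** The plan attaches no figure to this point. Its sample size of 140 is used below only to set the scale. That figure reproduces: going on if at least 15 of the first 46 families consent, and declaring success at 50 or more of 140 (a cut-off worked out here, not printed in the article), the exact one-sided type I error at 29% is 0.042 and the power at 40% is 0.800.

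**Order of events.** Topics are scored on the first meeting. Families often decide at the first approach, with up to 72 h allowed. The final decision is the model's outcome. For families who decide during the first meeting, predictor and outcome share one time window. For those who decide later, topic coverage comes first and the problem does not arise.

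**Illustration with no true topic effect.** From the article: 140 families and a 40% consent rate (the target rate in Statistical methods). Assumed, with no source in the article: a topic is covered in 80% of full conversations and in 30% of those ended early by refusal, and a share *e* of all families declines early.

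Shares of all families:
- consent, covered: 0.40 × 0.80 = 0.32
- consent, not covered: 0.40 × 0.20 = 0.08
- decline, covered: (0.60 − e) × 0.80 + e × 0.30
- decline, not covered: (0.60 − e) × 0.20 + e × 0.70

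At e = 0.20 the last two are 0.32 + 0.06 = 0.38 and 0.08 + 0.14 = 0.22. Consent is 0.32 / 0.70 = 46% with the topic and 0.08 / 0.30 = 27% without it. The odds ratio is (0.32 × 0.22) / (0.08 × 0.38) = 2.32.

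| e | decline, covered | decline, not covered | odds ratio | p < 0.05 | p < 0.20 |
|---|---|---|---|---|---|
| 0 | 0.48 | 0.12 | 1.00 | 5% | 20% |
| 0.05 | 0.455 | 0.145 | 1.27 | 9% | 28% |
| 0.10 | 0.43 | 0.17 | 1.58 | 20% | 45% |
| 0.20 | 0.38 | 0.22 | 2.32 | 56% | 81% |
| 0.30 | 0.33 | 0.27 | 3.27 | 88% | 97% |

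The last two columns are the share of simulated studies of 140 families in which a two-sided chi-square test falls below the limit. The predictor model may include more families, since the restriction to unregistered donors applies to the primary endpoint only.

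**A second set of assumptions.** Let a share *q* of refusals end the meeting before full coverage, with coverage otherwise *a*. The odds ratio is [a / (1 − a)] / [a(1 − q) / (1 − a(1 − q))]. For a = 0.80 and q = 0.20 this is 4 / (0.64 / 0.36) = 2.25. It is 1.56 at q = 0.10 and 3.14 at q = 0.30. At q = 0.20 it runs from 1.83 (a = 0.70) to 3.5 (a = 0.90).

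**Early agreement.** The first illustration cuts short refusals only. Keep e = 0.20, which is one third of decliners, and let some consenters agree early with the same 30% coverage. If one sixth of consenters do so, their coverage is (5/6) × 0.80 + (1/6) × 0.30 = 0.717, against 0.38 / 0.60 = 0.633 in decliners, and the odds ratio is (0.717 / 0.283) / (0.633 / 0.367) = 1.46. If one third do so, both groups have 0.633 and the odds ratio is 1.0. Beyond one third it falls below 1.

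**The case against.** The strongest objection is that the mechanism is inferred. The Background says that families often decide at the first approach; it does not say that the meeting then ends, and the remark covers agreement as well as refusal. With 72 h allowed, many decisions may follow a complete first meeting. All of this stands. It makes the size unknown, and if early agreement also skips topics the direction is open too. It does not remove the shared time window.

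A second objection is that the regression is exploratory and makes no causal claim about any topic. That limits the weight of the point, but the Discussion's aim of identifying important features of best practice invites a causal reading.

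A third is that the plan collects reasons for deviating from the pathway and reasons for the family's decision. These could help to identify topics missed because of a refusal, but neither is said to feed into the model.

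Stronger readings are tempting, and the article does not support them:
- *Adherence as a whole is distorted.* General meeting features are also recorded, and several core elements (designated requester, separation of the offer, deferral) precede the answer.
- *The adherence rate is understated because unreached topics count as failures.* The denominator and the coding depend on Table 1 and the case report form, which are not shown and may already allow for items that did not apply. Delivery over all events is also a legitimate rate in a pragmatic study.
- *Deferral to the requester suffers in the same way.* That element is already conditional, "If families raise the topic of organ or tissue donation, the managing health professional sensitively defers the first donation conversation to the designated requester", and comes before the conversation that a refusal might shorten.
- *Meeting time is a contaminated predictor.* The plan names it only as a variable to be summarised.

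**Conclusion.** The point holds for the topic-coverage items in the exploratory predictor analysis, and no further. They are measured in a window in which the decision is often made, are offered as candidate predictors of it, and have no stated safeguard. Under the assumptions shown, with 10% to 30% of families declining early, a topic with no effect would show an odds ratio of about 1.6 to 3.3. It would pass the p < 0.20 entry rule in about 45% to 97% of studies of 140 families, against 20% with no early decliners.

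Those figures illustrate a mechanism and do not estimate this study's bias: the early-decline share and both coverage rates are assumed, and only refusals are cut short. The primary endpoint and the sample size are not touched. A change to the analysis text is worth making because the plan as written could report a consequence of refusal as a predictor of consent.

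**What to change.** Under To address the secondary endpoints, build the main decision model only from adherence elements settled before the family responds: conversation led by a designated requester, offer separated from the conversation about death, planning before the meeting, and the meeting's structure and setting. Assign each item to its group from the case report form before the analysis.

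Report topic-coverage items descriptively by decision, or in a separate analysis labelled as open to reverse causation, and do not present them as predictors.

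The change is to analysis wording only. Its cost is that conversation-content items no longer compete in the main exploratory model, so the predictor endpoint says less about what is discussed and more about who leads the conversation and how it is arranged.
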